## Abstract

•CARDIS tests a co-created web-based support programme for cardiac arrest survivors.•CARDIS has a randomised controlled design with a waiting list control group.•Tailored content addresses emotional, cognitive, and physical needs.•Primary outcome is wellbeing and health at 3 months post-enrolment.•Process evaluation explores adherence, social selection, and participant engagement.

CARDIS tests a co-created web-based support programme for cardiac arrest survivors.

CARDIS has a randomised controlled design with a waiting list control group.

Tailored content addresses emotional, cognitive, and physical needs.

Primary outcome is wellbeing and health at 3 months post-enrolment.

Process evaluation explores adherence, social selection, and participant engagement.

## Introduction

Sudden cardiac arrest is a leading cause of premature death worldwide.^1^ Each year, approximately 300,000 out-of-hospital cardiac arrests (OHCA) occur in Europe, with survival averaging 7.5 %. In contrast, in-hospital cardiac arrest (IHCA) affects 1.5–2.8 per 1000 hospital admissions, with 30-day survival ranging between 27 % and 62 %.^2^

Most cardiac arrest survivors reported in clinical trials and registries are considered to have a favourable neurological outcome.^3^, ^4^, ^5^ However, survivors often face long-term cognitive, physical, psychological, and social sequelae, including impaired daily functioning and reduced health-related quality of life (HRQoL) that may persist for months or years.^6^, ^7^, ^8^, ^9^, ^10^, ^11^, ^12^ Many survivors of working age remain on long-term sick leave due to residual consequences.^13^ Psychological problems such as anxiety, depression, sleep difficulties, and post-traumatic stress disorder (PTSD) are common, affecting up to one in four survivors.^14^, ^15^, ^16^ Cognitive impairment and fatigue are also frequent,^5^, ^17^, ^18^, ^19^, ^20^, ^21^, ^22^ further limiting the ability to resume previous activities and work.^23^, ^24^ These consequences place a substantial burden on individuals, families, and society. Yet, survivors frequently encounter fragmented follow-up, insufficient rehabilitation, and difficulty accessing reliable information,^25^, ^26^, ^27^, ^28^, ^29^ with family members experiencing emotional distress as they take on caregiving responsibilities.^23^, ^30^ Education about recovery has been ranked as the most important intervention to reduce caregiver burden.^31^ Collectively, these complex problems highlight the need for holistic care models extending beyond initial survivorship to long-term rehabilitation and support. Structured rehabilitation has been shown to improve HRQoL and facilitate return to work.^13^, ^32^, ^33^, ^34^, ^35^, ^36^

Existing post-resuscitation care guidelines recommend follow-up within three months of hospital discharge to assess physical, emotional, and cognitive health.^37^, ^38^ However, studies in Sweden have shown that follow-up is inconsistent, and especially patients with non-cardiac causes of cardiac arrest, or IHCA survivors, often receive none at all.^39^ Similar shortcomings are evident internationally, where follow-up is frequently restricted to medical issues, while psychological, cognitive, and social needs remain unmet.^13^, ^27^, ^28^, ^40^, ^41^ As a result, limited understanding of cardiac arrest and its consequences can contribute to uncertainty and distress,^42^ and feeling unprepared for discharge may increase the risk of readmission among cardiac patients more broadly.^43^ Digital solutions could offer a complementary and cost-effective means of support and education, enhancing accessibility regardless of underlying cause of cardiac arrest, access to rehabilitation services, or place of residence.

Despite growing interest in digital health, web-based interventions tailored specifically for cardiac arrest survivors remain scarce. Current initiatives include ENFORCER in Italy, evaluating a structured one-year rehabilitation programme,^44^ STEPCARE in the UK and Sweden, testing a clinician-led psychoeducational intervention for cardiac arrest survivors and their key family members,^45^ and the dyad feasibility studies Recovering Together after Cardiac Arrest (RT-CA) in the US^46^ and CARESS in the UK.^47^ However, all these programmes rely on guided clinician-led on-line sessions or structured schedules. There remains a need for flexible digital solutions that accommodate individual recovery trajectories and diverse care contexts, enabling patients to engage at their own pace and according to individual needs.

**CARDIS** (**C**ardiac **AR**rest survivors **DI**gital **S**upport) is designed to address this gap. The multicentre randomised controlled trial (RCT) evaluates a co-created, user-friendly, self-guided web-based platform in Swedish, enabling survivors of both IHCA and OHCA – with or without a cardiac cause – to access tailored content, set personalised recovery goals, and engage with evidence-based health information and self-management strategies addressing emotional, cognitive, and physical consequences of cardiac arrest.

## Methods

### Co-creation of the intervention

The web-based support programme was co-created in 2024–2025, using an iterative and user-centred design approach,^48^ in collaboration with the Swedish HeartLung Association and the Swedish Network for Cardiac Arrest Survivors and their Relatives. This approach ensured that the needs and lived experiences of cardiac arrest survivors guided the development process. An overview of the co-creation process is illustrated in Fig. 1.

**Fig. 1 f0005:**
[figure not shown]
**Co-creation of the intervention**.

#### Needs assessment through interviews

Focus groups and individual interviews involving 20 participants (November 2024 to January 2025) explored survivors’ experiences, support needs, and preferences for digital solutions to complement existing follow-up care. Participants highlighted the importance of varied formats (images, short and easy-to-read texts, hyperlinks, videos), accessibility across devices (smartphones, tablets, and computers), and subtitled/multilingual content. Suggested key topics included facts about cardiac arrest, hospitalisation, life after cardiac arrest, common symptoms and limitations, existential concerns, treatment, lifestyle, intimacy and relationships, sleep, coping, return to work, and peer support. Participants also emphasised the need for dedicated content tailored to co-survivors and bereaved.

#### Content development

The research team, survivors and family members collaborated with experts in communication (web designer, photographer, and communicator) and cardiac arrest care (nurses and physicians in cardiology, intensive care and rehabilitation, physiotherapist, occupational therapist, rehabilitation coordinator, psychologist, dietician, and chaplain) to co-create the content and structure of the programme. Draughts of texts and videos were reviewed by experts and end users. Following this, individual interviews were conducted with five survivors and three family members to gather feedback on the clarity, relevance, and tone of the texts and videos, including language and phrasing. The material was subsequently revised in accordance with their suggestions to ensure that the content was perceived as meaningful, accessible, and appropriate for the target audience.

#### Final programme structure and technical implementation

The final version of the web-based support programme consists of four modules comprising 40 interrelated sections, addressing cardiac arrest and post-cardiac arrest care, physical recovery, psychological wellbeing, cognitive challenges, fatigue, intimate relationships, health behaviours and cardiovascular risk, and reintegration into daily life. One module targets co-survivors and children, also including bystanders and bereaved. Each module follows a consistent structure and includes written content, patient and family member narratives, short videos, images, animations, and links to validated external websites. Practical exercises are also suggested throughout the programme, such as mindfulness, breathing techniques, and strategies to reduce fatigue and promote physical activity. Additional features include support for creating an individual health plan and access to a moderated peer support chat forum (Fig. 2).

**Fig. 2 f0010:**
[figure not shown]
**Screenshot from the web-based support programme at****www.hjartstoppsoverlevare.se****, automatically translated from Swedish to English using GTranslate**.

Readability was enhanced using the Lix programme (https://www.lix.se/). Particular attention was paid to ensuring that texts, images, and videos reflect the diversity of survivors' life situations and personal needs. The primary language of the programme is Swedish. To enhance accessibility for non-Swedish speaking users, an automatic translation plugin (GTranslate) was integrated into the website, enabling multilingual functionality across >100 languages, covering over 99 % of global internet users.^49^ Only text-based content within the programme is automatically translated; embedded videos, patient narratives, and external links remain in their original language. The programme was developed in WordPress, hosted at https://www.hjartstoppsoverlevare.se (login required during study), and will later be publicly available via the national patient organisation website (https://www.hjart-lung.se/).

#### Feasibility study

A feasibility study (*n* = 6; median age 60; median time since cardiac arrest 42 months) was conducted in August 2025 to assess the usability, acceptability, and technical functionality of the web-based support programme. Using cognitive interviews and the think-aloud method,^50^ participants navigated the programme while verbalising their experiences, with a researcher present to prompt reflection.

Participants described the content as relevant, clear, and emotionally supportive. The System Usability Scale (SUS)^51^ yielded a mean score of 87/100, indicating a very high perceived usability. Users engaged with the programme sequentially, selecting content based on personal relevance. The programme was consistently described as trustworthy, relatable, and more engaging than conventional written materials. The module for co-survivors was particularly valued, enhancing understanding of their experiences during and after ICU care. Also, content on cognitive impairment, fatigue, PTSD, and anxiety was especially appreciated. Participants praised the intuitive design, readability, and calming visual elements. Participants with cognitive challenges found the layout accessible. Embedded videos supported users with mental fatigue and external links were perceived as credible. The option to translate the programme into multiple languages reinforced its inclusivity. Working-age participants highlighted the value of content on returning to work and navigating financial and bureaucratic systems. All participants stated they would recommend the programme to others, including healthcare professionals.

### Protocol

CARDIS is an investigator-initiated, clinically driven trial with no involvement or sponsorship from commercial entities. The study protocol was drafted according to SPIRIT guidelines.^52^, ^53^ Ethical approval was obtained from the Swedish Ethical Review Authority (ID: 2025-06113-01) and the study is registered at https://www.ClinicalTrials.gov (NCT07240714).

#### Overall aim

The overall aim of this study is to evaluate the effectiveness of a web-based support intervention for cardiac arrest survivors, focusing on self-reported wellbeing, health, and everyday functioning. In addition, a process evaluation will explore social selection bias, adherence, and participant experiences. Research questions are listed in Table 1.

**Table 1 t0005:** Research questions related to the effect and process evaluation of the digital support programme.

**Research questions related to the effect evaluation**
1. What impact does the intervention have on overall wellbeing and health?
2. How does participation affect self-reported HRQoL, cognition, life satisfaction, symptoms of anxiety and depression, PTSD, fatigue, and sleep disturbances?
3. To what extent does self-rated health literacy moderate the effect of the intervention?
4. What influence does the intervention have on general self-efficacy?
5. How does engagement with the intervention and self-management relate to self-reported healthcare utilisation and return to work or studies among individuals of working age?

**Research questions related to the process evaluation**

1. What level of adherence do participants demonstrate during the 3-months intervention period?
2. How adherent are participants in completing outcome measures at 3- and 6-months?
3. Are there differences in background characteristics between individuals who accept versus decline participation, and between those who complete versus discontinue the study?
4. How does self-rated health literacy correlate with adherence to the intervention?
5. How many eligible patients decline participation, and how many are excluded due to inclusion or exclusion criteria?
6. In what ways and how many minutes have participants in the intervention group engaged with the programme?
7. What experiences and perceived benefits are reported by participants who assessed the intervention?

### Study design and setting

CARDIS is a single-blinded (investigator blinded) parallel-group multicentre RCT. Participants will be recruited from eight sites with established post-cardiac arrest follow-up pathways. All participating sites will receive training to ensure that follow-up procedures align with standard care, as defined by current clinical guidelines.^37^, ^38^

Standard care includes screening and management of fatigue, cognitive function, and emotional and physical status, as well as providing information and support for survivors and their family members. As part of standard care, a printed informational booklet published by the Swedish Resuscitation Council^54^ is also provided. The booklet contains information on cardiac arrest, recovery, emotional and cognitive challenges, health-promoting behaviours, and available support resources.

The participating sites are located in regions with a combined population of approximately 6 million inhabitants, ensuring geographic and organisational diversity while supporting the feasibility of timely recruitment.

Based on historical data from the participating centres, the annual patient flow is expected to be approximately 350 patients, of which an estimated 30 % will be excluded due to eligibility criteria. Additionally, 30 % are expected to decline participation, leaving approximately 170 patients eligible for inclusion each year. The full sample size is therefore expected to be reached within 18 months of study initiation. Should recruitment proceed more slowly than anticipated, an extension of the enrolment period to 24 months will be requested.

### Eligibility criteria

Inclusion: ≥18 years of age, survived cardiac arrest 1–3 months prior to enrolment, access to internet-enabled device.

Exclusion: insufficient linguistic or cognitive ability to engage with the intervention or complete questionnaires designed in Swedish, or concurrent participation in another study collecting patient-reported outcome measures (PROMs) as primary endpoints.

### Study procedures

An overview of the study flow is illustrated in Fig. 3.

**Fig. 3 f0015:**
[figure not shown]
**Flowchart study procedure**. *Usual care = a printed informational booklet, one-time individual self-management advice, and standard post-cardiac arrest care as defined by current clinical guidelines.

### Recruitment and consent

Eligible patients will be identified by local healthcare professionals during routine follow-up 1–3 months post-discharge. Those meeting the eligibility criteria will receive verbal and written information about the study. Digital informed consent will be obtained by the national coordinator prior to data collection. Participants will be informed that participation is voluntary and that they may withdraw at any time without consequences for their care.

#### Randomisation

Participants will be randomised 1:1 to intervention or control using block randomisation stratified by site, ensuring balanced allocation within each site. Randomisation will be managed through REDCap (Research Electronic Data Capture), hosted at Linköping University. REDCap is a secure, web-based platform widely used in academic research for randomisation and electronic data capture.^55^, ^56^

The CARDIS trial is single-blinded. The national coordinator responsible for randomisation and survey distribution via REDCap is not blinded while data analysts and primary investigator will remain blinded to group allocation during data analysis. Allocation codes will be used in the exported dataset, and group identities will only be revealed after completion of all primary analyses. Participants and care providers are not blinded due to the nature of the intervention.

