### Outcomes and assessments

The primary outcome is overall wellbeing and health between the intervention and control groups 3 months after enrolment.

Secondary outcomes are self-reported HRQoL, life satisfaction, symptoms of depression and anxiety, PTSD, fatigue, cognitive impairment, sleep disturbances, and self-efficacy between the intervention and control groups 3- and 6-months after enrolment.

Assessments will be conducted at baseline, 3 months, and 6 months using self-reported validated digital questionnaires and study specific questions. Data completeness will be automatically monitored, and participants will receive regular reminders to ensure timely data entry. Variables are summarised in Table 3, Table 4.

**Table 3 t0015:** Data collection and assessments.

**Variables**	**Outcome measures**	**Baseline**	**3 months**	**6 months**

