### Sample size calculation and statistical analysis plan

The trial is planned to include 120 participants. A sample size calculation was conducted for the primary outcome variable (QWB). An a priori sample size calculation was conducted using G*Power for a repeated measures design with two groups and three time points (baseline, 3 months, and 6 months). Assuming a medium effect size (*f* = 0.25), a significance level of 5 % (*α* = 0.05), and a statistical power of 80 % (power = 0.80, corresponding to *β* = 0.20), the analysis showed that a total of 86 participants (43 per group) is sufficient to detect statistically significant differences between groups over time. To account for an estimated attrition rate of 30 %, a total of 120 participants (60 per group) will be recruited.

Baseline characteristics will be compared using chi-square, *t*-tests, or appropriate non-parametric methods. The intervention effect will be evaluated using linear mixed models (LMM) including fixed effects for time, group, and their interaction to assess differential changes over time between groups. Both random intercepts and slopes will be considered to account for individual variability in baseline levels and change over time.

All analyses will follow the intention-to-treat principle, whereby participants are analysed in their originally assigned groups regardless of adherence to the intervention.

There is no formally established minimal clinically important difference (MCID) for the QWB scale. However, previous research has shown that a total score below 50 is associated with clinically significant psychological distress.^58^ Effect sizes will be evaluated using marginal *R*^2^ and conditional *R*^2^.

Secondary outcomes will be analysed exploratorily. Although no formal power calculation has been conducted for these outcomes, their inclusion aims to provide a broader understanding of the potential effects of the intervention.

Adjustments for multiple comparisons, such as Bonferroni corrections, will be considered to control the risk of type I error.

No interim analyses are planned, as there are no anticipated safety concerns and the intervention does not involve clinical risk.

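### Randomisation is stratified by site but the described model has no site term, so the standard error of the 3-month between-group difference would be about 1 to 5% too large (minor)

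*Protocol article*

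**What the plan says.** - Protocol article, Randomisation: allocation is 1:1 by "block randomisation stratified by site, ensuring balanced allocation within each site".
- Protocol article, Study design and setting: "Participants will be recruited from eight sites with established post-cardiac arrest follow-up pathways".
- Protocol article, Sample size calculation and statistical analysis plan: the effect is to be evaluated with "linear mixed models (LMM) including fixed effects for time, group, and their interaction to assess differential changes over time between groups". On the random part: "Both random intercepts and slopes will be considered to account for individual variability in baseline levels and change over time".
- Protocol article, Outcomes and assessments: "The primary outcome is overall wellbeing and health between the intervention and control groups 3 months after enrolment".

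Site appears in neither the fixed nor the random part of the model, and the article does not say elsewhere that the stratification factor will be adjusted for.

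**The concern.** When allocation is balanced within strata, differences between strata contribute almost nothing to chance imbalance between the arms. The true sampling variance of a between-group difference is then smaller than the total outcome variance implies. A model that leaves out the strata does not know this: it keeps the between-site variation in its error and reports a standard error larger than the design delivers. The trial takes the trouble to stratify but, as described, would not collect the precision.

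Site differences in level are plausible. The Study design and setting section stresses the geographic and organisational diversity of the sites, and the Introduction reports inconsistent follow-up in Sweden. At stake are a slightly wide interval and a little lost power for the 3-month comparison. Validity is not at stake.

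**Working it through.** **Inputs from the article.** Eight sites; 120 recruited (60 per group); 30% attrition; f = 0.25; alpha 0.05; power 0.80; three visits; 86 evaluable.

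**Assumptions (not in the article).** Correlation between visits 0.5; total variance at each visit 1; site share of variance s = 0.02, 0.05 or 0.10; 15 participants per site, split 8 to 7.

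**1. The plan's own figure.** For a repeated-measures between-factor test, the noncentrality is λ = f² × N × m / (1 + (m − 1)ρ). With m = 3, ρ = 0.5 and N = 86, λ = 0.0625 × 86 × 3 / 2 = 8.06. On 1 and 84 degrees of freedom the power is 0.801, and 86 is the smallest even N that reaches 0.80. The within-between interaction test at the same correlation would need only 28. So 86 matches a between-group comparison, the kind of contrast that omitting site affects. With 30% attrition, 120 × 0.7 = 84 evaluable, and power is 0.792.

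**2. Between-group difference at 3 months, no dropout.**

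- Without site: SE = √(1/60 + 1/60) = 0.1826.
- With a site main effect in the three-visit random-intercept model, the contrast splits into a person-mean part, adjusted for site, and a within-person part, where site cancels. The information is 8 × (7 × 8/15) = 29.87 for the first and 60 × 60/120 = 30 for the second. So SE² = (0.5 − s + 0.5/3)/29.87 + (0.5 × 2/3)/30.

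| s | SE without site | SE with site | Excess | Excess with 30% dropout |
|---|---|---|---|---|
| 0.02 | 0.1826 | 0.1810 | 0.9% | 0.8% |
| 0.05 | 0.1826 | 0.1782 | 2.5% | 2.1% |
| 0.10 | 0.1826 | 0.1734 | 5.3% | 4.8% |

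The simple formula 1/√(1 − s), which assumes exact balance, gives 1.0%, 2.6% and 5.4%. The dropout column comes from generalised least squares on simulated dropout patterns.

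**3. Size of the test.** With site omitted, the real size of a nominal 5% test is 2Φ(−1.96/√(1 − s)), or 4.8%, 4.4% and 3.9%. It lies below 5% throughout.

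**4. Power, at the plan's own operating point.** At N = 84, λ = 0.0625 × 84 × 3 / 2 = 7.875 and √λ = 2.806. By normal approximation, power is Φ((2.806 − 1.96)/√(1 − s)) without site and Φ(2.806/√(1 − s) − 1.96) with it:

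- s = 0.02: 0.804 against 0.809, a gain of 0.5 points.
- s = 0.05: 0.807 against 0.821, a gain of 1.4 points.
- s = 0.10: 0.814 against 0.841, a gain of 2.7 points.

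This translates the precision loss into power near 80%. It is not a separate power calculation for the 3-month contrast.

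**5. Group-by-time coefficient at 3 months.** This is a difference between groups in within-person change, so a constant site effect subtracts out. Its SE is √(2(1 − 0.5) × 2/60) = 0.1826 with or without a site main effect: ratio 1.000 without dropout, and 0.9998 to 1.0012 with 30% dropout. It improves only if sites differ in change over time and site-by-visit is fitted. The SE then falls from 0.1826 to 0.1793 at a site-by-time variance of 0.02 (excess 1.8%) and to 0.1736 at 0.05 (excess 5.2%).

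**The case against.** The strongest objection is that the article does not exclude site. The listed terms follow the word including, the article condenses a fuller plan, and stratification covariates are often left to the SAP. That stands in part: the full plan may already contain site, and then one sentence closes the point. But the section names both the fixed and the random part of the model and neither holds the stratification factor, so the comment is on a described model.

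The second objection is that the effect is to be assessed through the time-by-group interaction, where constant site differences cancel. This stands in full. A reader might infer that all the model's standard errors are too large; the article does not support that. What remains is the between-group difference at 3 months, which is how the primary outcome is worded.

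Third, the site share of variance is assumed, and training all sites to align follow-up may keep it small. This also stands, although training does not remove differences in case mix.

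A reader might also infer that leaving out site departs from analysing as randomised. It does not: the article commits to intention-to-treat, and omitting a stratification factor is a matter of precision.

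**Conclusion.** The point holds, and it is minor. As described, the model lacks the factor by which randomisation was stratified. For the 3-month between-group difference, its standard error would be about 1%, 2.5% or 5% too large if site explains 2%, 5% or 10% of outcome variance. The cost is roughly 0.5 to 3 power points. There is no bias and no type I inflation, and the stated sample size is not affected. The group-by-time coefficient is untouched unless sites differ in change over time.

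These sizes rest on assumed site shares, a correlation of 0.5 between visits and near-equal sites, none of which the article gives. The direction, a reported error too large rather than too small, depends only on allocation being close to balanced within sites and on sites differing in level.

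**What to change.** Include site as a fixed effect with eight levels in the primary model, and report the 3-month between-group contrast from that model. Add site-by-visit only if it is pre-specified, and state in advance how very small sites will be pooled. If the full analysis plan already includes site, say so in the article's model description.

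The cost is 7 degrees of freedom for the site main effect and 7 × 2 = 14 more if site-by-visit is added. With about 84 evaluable participants, or 84/8 = 10.5 per site on average, the main effect is easily affordable. The 14 further terms are worth having only if sites are expected to differ in recovery. The Trial status section places the start of recruitment in autumn 2026, so the change can be written in before then.
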